### Statistical method

The main analyses will be by intention to treat, taking into account the patients in each group according to the initial assignment to the study groups, regardless of the compliance with the program by the patient or the responsible physicians, or any other pharmaceutical adequacy intervention that the physicians or patients in the control group may receive.

We will first describe the baseline characteristics of the sample and compare the intervention and control groups to assess baseline comparability. Although the intervention is mainly directed at the prescribing physician through recommendations or suggested changes, outcomes will be assessed at the individual patient level. We will account for potential non-independence of observations arising from patients being managed by the same physician (cluster effect).

Primary outcome variables include: number of DRPs per patient, proportion of patients with DRPs, number of medications per patient, and proportion of polymedicated patients. The effects of the intervention on dichotomous outcomes will be assessed using multilevel mixed-effects logistic regression models (cluster-adjusted), with the odds ratio (95% CI) of the intervention group *versus* control serving as the measure of effect. For continuous variables, we will use linear mixed-effects regression models (cluster), calculating differences between adjusted means (95% CI) between the intervention and control groups. Statistical significance will be set at p < 0.05.

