As part of the Program for chronic care management developed by the Catalan department of health (Departament de Salut, 2015), the Basic guide for medication management in chronic patients was published (Departament de Salut, 2013). This guide outlines a methodology for treatment optimization through patient-centred, multidisciplinary medication review procedures involving reconciliation, review, deprescribing, and adherence strategies.

In this context, the Primary care directorate of the Camp de Tarragona region (Catalan health institute) oversees 24 nursing homes linked to 20 primary care teams, serving a total of 1,928 residents in 2022. Within this policy framework, a pharmaceutical care program was launched in nursing homes with the aim of reducing DRPs and improving medication safety.

This abstract presents the study protocol, which aims to evaluate the effectiveness of a pharmacist-led intervention to optimize medication use in nursing home residents.

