### Design

This is a quasi-experimental study using a non-randomized cluster assignment of patients (nursing homes) into two groups: (a) an intervention group receiving a structured review and optimization of pharmacotherapeutic plans, and (b) a control group receiving usual care based on standard clinical practice (Figure 1).

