### Assignment to study groups

Clustering was defined at the level of the nursing home to minimize the risk of contamination, as residents within the same facility are typically treated by the same medical and care teams. Assigning entire centers to either the intervention or control group also facilitated the coordinated implementation of the structured medication review process and aligned with the organizational routines of the participating facilities.

Assignment to either the intervention or control group will be based on convenience within the context of implementing the pharmaceutical review program in the study area. The first 12 nursing homes in which the program is implemented will be allocated to the intervention group, with the remaining nursing homes forming the control group. The comparability of the groups will be ensured in terms of nursing home characteristics (geographical location, size, organizational and healthcare features) and patient profiles (sociodemographic and clinical variables.

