## Statistical methods

### Sample size

Based on prior observations and published studies, we assume that the proportion of patients with drug-related problems (DRPs) will be 50% in the control group (Vink et al., 2011; Costa et al., 2016; Garin et al., 2021). We expect to detect an absolute reduction of 10 percentage points in the prevalence of medication-related problems, from 50% in the control group to 40% in the intervention group. This difference is considered clinically meaningful, as even a modest reduction in such problems may lead to significant improvements in patient safety and care quality in the nursing home setting.

The sample size is calculated to account for the cluster design of the study, using the GRANMO calculator (https://www.datarus.eu/en/applications/granmo/). Assuming an alpha risk of 0.05 and a power of 0.80 in a two-sided test to detect a difference between proportions of 0.50 in the control group and 0.40 in the intervention group, a total of 24 clusters (12 per group) with 37 participants per cluster is required, including an estimated 10% loss to follow-up. A low intraclass correlation coefficient (ICC) of 0.001 is assumed. In the absence of published ICC estimates for this setting, we adopt a conservative value consistent with other studies involving individual-level binary outcomes with limited clustering. If the actual ICC or the number of participants per cluster differs substantially from expectations, we will conduct a sensitivity analysis to assess the potential impact on statistical power and precision.

Participants who die during the follow-up period will be considered lost to follow-up and excluded from outcome analyses. This expected attrition has been accounted for in the sample size calculation, which includes an estimated 10% loss due to mortality and other causes of dropout.

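### The analysis names the physician as the source of clustering, while nursing homes are assigned and sized as the clusters; a physician-only model could understate standard errors

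*Protocol article*

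**What the plan says.** Three sections of the protocol article make the nursing home the cluster.

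- Design describes a "non-randomized cluster assignment of patients (nursing homes) into two groups".
- Assignment to study groups states: "Clustering was defined at the level of the nursing home to minimize the risk of contamination". It continues: "The first 12 nursing homes in which the program is implemented will be allocated to the intervention group"; the remaining homes are controls.
- Sample size concludes that "a total of 24 clusters (12 per group) with 37 participants per cluster is required", with a two-sided alpha of 0.05, power of 0.80, an ICC of 0.001 and 10% loss.

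The Statistical method section then describes the analysis. Its only statement of what the cluster effect is reads: "We will account for potential non-independence of observations arising from patients being managed by the same physician (cluster effect". The next paragraph lists four primary outcomes. It prescribes mixed-effects logistic models for the two binary outcomes and linear mixed models for the continuous ones, with cluster adjustment mentioned in brackets and no level named. A nursing-home effect does not appear.

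Two further statements bear on how far physician and home overlap. Assignment to study groups says that "residents within the same facility are typically treated by the same medical and care teams". The Introduction says that the regional directorate "oversees 24 nursing homes linked to 20 primary care teams, serving a total of 1,928 residents in 2022".

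**The concern.** The group contrast varies only between homes, because every resident of a home carries the same assignment. Its variance therefore has to include the variance between homes. A model with a random intercept for physician alone treats two physicians in one home as independent replicates of the treatment condition. Any home-level variance is then averaged over the number of physicians rather than over 12 homes per group, and the standard error comes out too small.

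This is not detail left to an analysis plan. The article does state a source of clustering, and it is not the unit that was assigned. An analyst who followed the sentence literally would fit a physician effect. Because the sentence governs the models for all four primary outcomes, every confidence interval and every test at p < 0.05 depends on how it is read.

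**Working it through.** **Step 1: which level was used for the sample size.** Inputs from Sample size: proportions 0.50 and 0.40, two-sided alpha 0.05, power 0.80, ICC 0.001, 10% loss, 12 homes per group.

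- Individually randomized size, pooled formula: n = [1.96 × √(2 × 0.45 × 0.55) + 0.8416 × √(0.25 + 0.24)]² / 0.10² = 387.4, so 388 per group.
- Residents analysed per home: m = 37 × 0.9 = 33.3.
- Design effect: 1 + (33.3 − 1) × 0.001 = 1.0323.
- 388 × 1.0323 = 400.5; 400.5 / 0.9 = 445.0 per group; 445.0 / 12 = 37.1 per home.

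This matches the stated 37. The sizing is at home level.

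**Step 2: effect of a physician-only model.** Let ρ be the home-level ICC and J the number of physicians per home, each nested in one home. The article gives no J, and no ICC other than 0.001, so all other values are assumptions.

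- Correct variance of a group mean is proportional to 1 + (m − 1)ρ.
- Variance that a physician-only model works with is proportional to 1 + (m/J − 1)ρ.
- SE ratio: r = √{[1 + (m − 1)ρ] / [1 + (m/J − 1)ρ]}.
- Type I error: 2 × [1 − Φ(1.96 / r)].

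Worked case, ρ = 0.05 and J = 2: numerator 1 + 32.3 × 0.05 = 2.615; denominator 1 + 15.65 × 0.05 = 1.7825; r = √1.467 = 1.211; 1.96 / 1.211 = 1.618; type I error 10.6%.

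| Home ICC | J = 1 | J = 2 (r) | J = 3 (r) |
|---|---|---|---|
| 0.001 (plan) | 5.0% | 5.2% (1.008) | 5.3% (1.011) |
| 0.01 (assumed) | 5.0% | 6.7% (1.070) | 7.4% (1.096) |
| 0.02 (assumed) | 5.0% | 8.0% (1.120) | 9.4% (1.170) |
| 0.05 (assumed) | 5.0% | 10.6% (1.211) | 13.7% (1.318) |

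**Step 3: check by simulation.** A balanced linear model was simulated with 12 homes per group, no true effect, 20,000 runs and a t reference. With home-level variance only and a physician-only model, the rejection rate for J = 2 and J = 3 was 7.3% and 9.1% at ICC 0.02, and 10.9% and 13.5% at ICC 0.05. With the random effect at home level it was 4.7-5.4% in all scenarios. With no home-level variance beyond the physician (physician ICC 0.02), the physician-only model held its level at 4.8-4.9%. The logistic models were not simulated.

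**The case against.** The strongest reply is that a physician-only model is never prescribed. The article does not mention a random intercept for physician and does not exclude one for home. Elsewhere in the article the cluster is the nursing home, so the bracketed cluster adjustment can be read that way, and a multilevel model leaves room for physician within home. This stands in part. The physician reading is the natural one, because it is the cluster effect defined just before the models, but it is not explicit.

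A second reply is that physician and home may largely coincide, since residents of a facility usually share a medical team. With one physician per home there is no inflation at any ICC. With 20 primary care teams for 24 homes, a physician might even cover several homes. Physician clusters could then be as large as homes or larger, or could cross the two groups, so the direction of the error is not fixed. This also stands. Against it, the Intervention section speaks of responsible physicians in the plural, and Usual care distinguishes nursing home physicians from the primary care physicians who authorize treatment. Several physicians per home is therefore plausible but undocumented, and it is unclear which physician the analysis sentence means.

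A third reply is that every sizeable figure uses an ICC 10 to 50 times the plan's 0.001. That is correct. Yet 0.001 is itself an assumption: the article reports no published estimate for this setting and foresees that the actual value may differ. The sensitivity analysis it promises for that case concerns power and precision and would not correct the model level.

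A reader might also fault the lack of small-sample degrees of freedom with only 24 homes. That is commonly left to the analysis plan, which is not shown, and is no part of this point.

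**Conclusion.** The inconsistency is established from the text: homes are assigned and sized as clusters, and the only cluster effect named for the analysis is the physician.

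A reader might infer that the standard errors will be too small and that type I error will exceed 5%. The documents do not support that as a certainty. It requires a physician-only model, more than one physician per home, and home-level variance beyond the physician, and none of the three is documented. Under those conditions, with 2 to 3 physicians per home, type I error is about 7% at a home ICC of 0.01, 8-9% at 0.02 and 11-14% at 0.05. At the plan's ICC of 0.001 it is 5.2-5.3%. The figures rest on equal cluster sizes, physicians nested within homes, and a linear model or normal approximation.

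The sentence should be changed before analysis. A home-level effect keeps the variance at the level of assignment whatever the staffing or the true ICC turns out to be.

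**What to change.** In the Statistical method section, replace the sentence on physician clustering with:

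> All models include a random intercept for nursing home, the unit of assignment; physician may be added as a further level.

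This brings the analysis into line with Design, Assignment to study groups and Sample size. It needs no new data on the group contrast, only the home identifier already used for assignment.

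The cost is one sentence and possibly wider confidence intervals. Relative to a physician-only model with 2 to 3 physicians per home, the widening is the SE ratio above: about 1% at an ICC of 0.001, 7-10% at 0.01, and 21-32% at 0.05. That width is the uncertainty the physician-only model would have left out.

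### Four unranked primary outcomes are all judged at p < 0.05, only one was used for the sample size, and the protocol does not say which result decides effectiveness

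*Protocol article*

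**What the plan says.** In the protocol article, the Statistical method section gives the list: "Primary outcome variables include: number of DRPs per patient, proportion of patients with DRPs, number of medications per patient, and proportion of polymedicated patients". It assigns mixed-effects logistic models to the two yes/no outcomes and linear mixed models to the two counts, and closes with one rule for all: "Statistical significance will be set at p < 0.05".

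The Sample size section works with one of the four. Its starting point is "we assume that the proportion of patients with drug-related problems (DRPs) will be 50% in the control group", with a change "from 50% in the control group to 40% in the intervention group", and its error rates are given as "Assuming an alpha risk of 0.05 and a power of 0.80 in a two-sided test". The result is "a total of 24 clusters (12 per group) with 37 participants per cluster is required, including an estimated 10% loss to follow-up".

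The Abstract (Expected results), the Objective section and the Measurement section repeat the same two domains, each as a per-patient number and as patients affected. None of them ranks the four measures.

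**The concern.** The Objective section poses one overall question, whether the intervention is effective, and divides it into DRPs and polypharmacy. Four primary outcomes then bear on that question, each judged at 0.05, and the sample size allots the whole 0.05 to one of them. A reader cannot tell whether one significant result is enough, whether one per domain is needed, or whether all four must succeed.

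The ambiguity has practical consequences because the outcomes come in pairs. By the definitions in the Measurement section, polymedicated status is the medication count cut at 10 or more, and having a DRP is the DRP count cut at one or more. If the count and its yes/no version disagree, nothing says which governs. Outcome assessment is unblinded and is done by the pharmacist who delivers the intervention, so a prior statement of the deciding outcome is worth more here than usual.

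**Working it through.** **Inputs from the article.** Four primary outcomes; threshold 0.05; two-sided alpha 0.05 and power 0.80; 0.50 against 0.40; 12 homes per group; 37 residents per home; 10% loss; ICC 0.001 ("A low intraclass correlation coefficient (ICC) of 0.001 is assumed").

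**Assumed inputs.** The correlations between the four test statistics, and the rule that any one significant result counts as success. The article gives neither.

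**1. The plan's own sample size.** With pooled variance and mean proportion 0.45:

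n = [1.960 × √(2 × 0.45 × 0.55) + 0.842 × √(0.50 × 0.50 + 0.40 × 0.60)]² / 0.10² = 387.3, so 388 per group.

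- Residents per home after loss: 37 × 0.9 = 33.3.
- Design effect: 1 + (33.3 − 1) × 0.001 = 1.0323.
- Inflated size: 388 × 1.0323 / 0.9 = 445 per group, or 37.1 per home.

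The article's 12 × 37 = 444 per group (888 in all) is reproduced closely. This confirms that the whole two-sided 0.05 is used on the proportion of patients with DRPs.

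**2. At least one false positive among four tests, no true effect.** Under independence: 1 − 0.95⁴ = 0.185. Otherwise by simulation of four correlated two-sided z-tests, 1,000,000 draws. The last column counts only false results that favour the intervention; under independence it is 1 − 0.975⁴ = 0.096.

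| Assumed correlation | Either direction | Benefit only |
|---|---|---|
| 0 throughout | 18.5% | 9.6% |
| 0.3 throughout | 17.4% | 8.7% |
| 0.5 throughout | 15.6% | 7.8% |
| 0.7 throughout | 13.1% | 6.5% |
| 0.8 throughout | 11.4% | 5.8% |
| 0.9 throughout | 9.4% | 4.7% |
| 0.7 within pairs, 0.2 across | 15.8% | 8.0% |
| 0.7 within pairs, 0.5 across | 14.6% | 7.3% |
| 0.8 within pairs, 0.2 across | 14.8% | 7.5% |
| 0.8 within pairs, 0.5 across | 13.8% | 6.9% |

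A single test gives 5% and 2.5%. The last four rows fit the outcomes best, because each yes/no outcome is a cut of its count. Simple data models support the within-pair range: a Poisson count with about half of patients at zero correlates 0.83 with its yes/no version, an overdispersed count 0.68, and a medication count cut at 10 about 0.80.

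**3. The opposite rule.** If all four had to be significant, type I error would not be inflated. Power for the joint result could not exceed the 80% planned for the sized outcome, and would generally be lower. The other three have no stated power.

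**4. Cost of the possible remedies.**

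- *One primary outcome, or a fixed order starting with the sized outcome:* type I error is 5%. The effective size is 444 × 0.9 / 1.0323 = 387 per group, with power 80.0%. The 888 stands.
- *Bonferroni over four (0.0125 each):* power for the sized outcome falls to 61.8%. Restoring 80% needs 551 per group before inflation. After inflation this is 551 × 1.0323 / 0.9 = 632 per group. At about 48 evaluable residents per home the design effect is 1.047, giving 551 × 1.047 / 0.9 = 641. The total is about 1,264 to 1,282.

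**The case against.** The strongest reply is that the article never says one significant outcome is enough. The Objective section states two aims with two measures each, and the Abstract's expected results join the measures within each aim, which could mean that both are required. If all four must succeed, there is no inflation. If each aim is its own question with two tests, the two-sided error per aim is about 8% at a correlation of 0.7 to 0.8. This stands: the figures above are conditional on a rule the article does not state, and the finding is that the rule is missing.

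A reader might infer that the trial has a 13% to 19% chance of falsely claiming effectiveness. The article does not support that. Those figures count errors in both directions, and a significant result favouring control would not be reported as effectiveness; in the benefit direction the corresponding range is 6.5% to 9.6%. The upper end also needs independent tests, which is implausible when two outcomes are cuts of the other two.

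It can also be said that a testing order or alpha split usually sits in an analysis plan, which is not shown, so an adjustment may exist. That is fair as to detail. But the article itself fixes four primary outcomes, one threshold, and a sample size that leaves no alpha for three of them. An alpha split made elsewhere would conflict with the Sample size section. Sizing on one of several outcomes is not in itself an error.

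Finally, allocation by convenience and unblinded assessment mean that curing multiplicity would not secure a true 5% error rate. That is correct, and it limits what the fix achieves without removing the need for it.

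**Conclusion.** The point holds in a limited form. The protocol lists four unranked primary outcomes at 0.05 each, sizes the trial on one with the full two-sided 0.05, and does not say which result decides effectiveness.

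If any one significant outcome were accepted, at least one false-positive primary result would be expected in about 14% to 16% of such trials with no true effect, and one in favour of the intervention in about 7% to 8%. This rests on assumed correlations. Over the wider span considered, the two-sided figure runs from about 9% (0.9 throughout) to 18.5% (independence), against 5% for one test. The figures cover multiplicity only and say nothing about bias from non-random allocation or unblinded assessment.

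**What to change.** Before outcome data are analysed, name the proportion of patients with at least one DRP as the single primary outcome, tested at two-sided 0.05. Make the number of DRPs, the number of medications and the proportion of polymedicated patients secondary. Test them in a stated fixed order, or with Holm, only if the primary result is significant. Date and record the change: parts of the article describe data collection in the past tense, and a choice made after seeing results would carry little weight.

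The cost is about two sentences. The planned 24 × 37 stays as it is under the article's own assumptions, including the ICC of 0.001. The small downside is that claims on the other three outcomes become conditional. Making the number of DRPs primary instead would need a new power calculation, and the article gives no variance for it.

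### The stated 80% power makes no allowance for having only 24 homes: on the protocol's own inputs it is about 76% to 77% against t with 22 df, and the reference distribution for the tests is left open

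*Protocol article*

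**What the plan says.** In the Sample size section the protocol article sets the test and its target: "Assuming an alpha risk of 0.05 and a power of 0.80 in a two-sided test". The effect to be detected is "a difference between proportions of 0.50 in the control group and 0.40 in the intervention group". The result is that "a total of 24 clusters (12 per group) with 37 participants per cluster is required", "including an estimated 10% loss to follow-up". On clustering: "A low intraclass correlation coefficient (ICC) of 0.001 is assumed". The same section says that no published ICC exists for this setting, and promises a sensitivity analysis of power and precision if the ICC or cluster size turns out differently.

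The Statistical method section names mixed-effects logistic models for binary outcomes and linear mixed models for continuous ones, both with 95% confidence intervals, and closes with "Statistical significance will be set at p < 0.05". It gives no reference distribution, estimation method or degrees-of-freedom rule.

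The two sections also differ on the cluster. Under Assignment to study groups, "Clustering was defined at the level of the nursing home to minimize the risk of contamination". Under Statistical method, the dependence to be allowed for comes from "patients being managed by the same physician (cluster effect".

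**The concern.** Whole homes are assigned to a group, so the group effect is a contrast between homes. With 24 homes and two groups, it carries 24 − 2 = 22 degrees of freedom, however many residents each home supplies. A design effect inflates the variance for within-home correlation. It does not account for having to estimate the between-home variance from 24 units.

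Two things are at stake. First, the power quoted as the justification for the sample size may not be reached even at the very small ICC assumed. Second, if the mixed models are read against the normal distribution and homes differ more than planned, the tests will reject too often and the 95% intervals will cover too little. The promised sensitivity analysis concerns power and precision, not whether the test keeps its level.

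**Working it through.** **Inputs (Sample size section):** p₁ = 0.50, p₂ = 0.40, two-sided α = 0.05, power 0.80, 12 homes per group, 37 recruited per home, 10% loss, ICC 0.001. Analysed per home: 37 × 0.9 = 33.3. The 22 degrees of freedom take the home as the cluster, as in Assignment to study groups.

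**1. Reproduce the stated sample size.**
- Pooled normal formula: n = [1.96 × √(2 × 0.45 × 0.55) + 0.842 × √(0.25 + 0.24)]² / 0.10² = 387.3, so 388 per group.
- Design effect: 1 + (33.3 − 1) × 0.001 = 1.0323.
- 388 × 1.0323 = 400.5; 400.5 / 0.9 = 445 per group; 445 / 12 = 37.1 per home, against 37 stated.
- The unpooled formula gives 36.8 per home. With a continuity correction it is 39.0, which does not match.

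The figure therefore comes from normal quantiles and a design effect alone.

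**2. Power with 22 degrees of freedom.**
- Effective number per group: 12 × 33.3 / 1.0323 = 387.1.
- Standard error: √(0.49 / 387.1) = 0.03558; ratio 0.10 / 0.03558 = 2.811.
- Normal: Φ(2.811 − 1.960) = 80.3%.
- Non-central t, 22 df, critical value 2.074: 76.6%.
- With the pooled variance (0.495 in place of 0.49): 79.9% by z and 76.2% by t. On the log-odds scale, t gives 76.1%.

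Reaching 80% against t with 22 df needs about 36.8 analysed per home, or 36.8 / 0.9 = 40.9, so 41 recruited.

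**3. Check by simulation** (24 homes, 33 residents each, beta-binomial home effects, maximum-likelihood random-intercept logistic model, 3,000 trials per run, Monte Carlo error about 0.4 points for type I error).
- Power at ICC 0.001: home-level t test 75.8%; logistic mixed model 78.6% with z and 74.3% with t on 22 df.
- Power at an assumed ICC of 0.01: the t formula gives 65% to 66%; the simulated home-level t test gives 66.6% and the logistic model with t 67.6%.

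**4. Type I error if Wald z were used.** In the limit where between-home variation dominates, P(|t₂₂| > 1.96) = 6.3%. With the maximum-likelihood variance, which is too small by 22/24, it is P(|t₂₂| > 1.96 × √(22/24)) = 7.4%. Simulated rates for the logistic mixed model:

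| ICC | Wald z |
|---|---|
| 0.001 (protocol) | 3.7% to 4.9% |
| 0.005 (assumed) | 4.7% to 5.5% |
| 0.01 (assumed) | 5.9% to 6.6% |
| 0.02 (assumed) | 6.6% |
| 0.03 (assumed) | 6.6% to 6.9% |
| 0.05 (assumed) | 6.2% to 7.9% |

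For a normal outcome under REML, z gives 5.6% at ICC 0.01 and 6.2% at 0.05. Taken together, the rate is about 5.5% to 7.4% for ICCs of 0.01 to 0.05; the single run at 7.9% lies little more than one Monte Carlo error above that range. For ICCs of 0.01 and above, t with 22 df gives 4.4% to 6.6% in the logistic model, and the home-level t test 4.4% to 5.8%.

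**5. Interval width.** 2.074 / 1.960 = 1.058, so about 6% wider.

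**The case against.** A reader might infer that this trial will exceed its 5% error rate and report intervals that are too narrow. The document does not support that. The sentence on significance sets a threshold and nothing more, and the article neither prescribes nor rules out a z test. A condensed article may leave the degrees-of-freedom method to an analysis plan, so its silence is not an error in itself. At the protocol's own ICC, z-based mixed models are not inflated. Inflation needs both z inference and an ICC of about 0.01 or more, a value that the document does not give.

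It is also fair to say that the two effects belong to different settings. The 76% to 77% applies at ICC 0.001, where z would keep its level and simulated power by z is 78.6%. Part of the shortfall there is the price of using t where it is mildly conservative. Where z does inflate, at ICC 0.01, power against t is already only about 65% to 67%. The size of the ICC therefore matters more than the choice of reference distribution, and the protocol already promises a sensitivity analysis on it.

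Finally, 22 is not a settled number. It presumes a home-level random effect, while the analysis section names the physician, and the Discussion foresees statistical adjustment for imbalances, which could bring in home-level covariates and leave fewer degrees of freedom.

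These points limit the false-positive half to a conditional caution. They do not remove the power half. The 80% is a stated figure, it was obtained without allowance for 12 homes per group, and the home-level t test, which holds close to 5% at ICC 0.001 (4.5% to 5.0% in simulation), reaches about 76%.

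**Conclusion.** The point holds in limited form. The stated 80% power is optimistic by up to about 4 points on the protocol's own inputs: about 76% to 77% when the group effect is tested against t with 22 df. This rests on the home being the cluster, on equal cluster sizes and on the full 10% loss; with no loss, all 37 per home would give 80% to 81%.

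The false-positive risk is conditional. With Wald z, the level is kept at the planned ICC of 0.001 and would rise to about 5.5% to 7.4% at ICCs of 0.01 to 0.05. Those ICCs are assumptions, but they cannot be dismissed when the protocol itself has no published estimate and says that residents of a home usually share their medical and care teams. Since default mixed-model output may rely on z, the choice deserves to be fixed in advance.

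**What to change.** In Sample size, restate the power as about 76% to 77% at ICC 0.001 and say that it is lower at larger ICCs (about 65% to 67% at an assumed 0.01). Alternatively, recruit about 41 per home in place of 37. That is 24 × 41 = 984 residents against 888. The 1,928 residents reported for 2022 average about 80 per home, but the article does not give the number eligible in each. Adding homes is not open, because all 24 are already in the study.

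In Statistical method:
- Name the nursing home as the cluster in the models, consistent with Assignment to study groups.
- For the linear mixed models, specify REML with Kenward-Roger or Satterthwaite degrees of freedom.
- For the logistic mixed models, test the group effect and form its interval with t on the between-home degrees of freedom: 22, or fewer if home-level covariates are added.
- Add a t test on home-level summaries as a check. A permutation test is not a natural choice here, because homes are allocated by convenience and not at random.

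The cost is a few sentences and a software option, intervals about 6% wider, mild conservatism if the ICC is truly near zero, and a slightly lower stated power.
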